### Statistical methods

Comparisons between two intervention groups are analysed with independent samples t-test, Mann Whitney U-test or Pearson Chi-square as applicable. If possible, logarithmic transformation for non-normal variables is performed in order to achieve normal distribution. The impact of vitamin D supplementation, and relevant covariates, on serum 25-hydroxyvitamin D concentration is analysed with linear mixed model. For continuous variables (bone strength), differences between intervention groups are assessed with multivariate analysis of covariance (MANCOVA). For evaluating the effect of vitamin D supplementation on the frequency of infections, negative binomial model is applied. Infection incidence is estimated as proportion of follow-up time as person-months allowing utilisation of all available data. Main outcome measures are analysed according to intention-to-treat and protocol-based manner.

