### Primary outcomes

Primary outcomes of the study are bone strength measured by peripheral quantitative computed tomography (pQCT) and incidence of parent-reported infections at age 2 years.

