### **Follow-up**

Participants are assessed at a study outpatient clinic by a study nurse and/or pediatrician at 6 months, 1 year and 2 years of age. Growth parameters (length, weight, head circumference) are measured and compared with Finnish growth charts. Blood samples are taken for biochemistry. Bone strength of participants is evaluated by pQCT at 1 and 2 years of age. Families are provided study diaries where they keep daily records on dosing of vitamin D3 supplement and on all infections of the participating child. Nutrient intake from food is evaluated from 3-day food record at 1 year and a Food Frequency Questionnaire (FFQ) at 2 years of age.

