## STATISTICAL ANALYSIS PLAN

### Sample size calculation and statistical analyses

We aim at detecting a 0.2 SD unit difference between continuous bone strength parameters; bone mineral content and cross-sectional area. In order to reach a statistical power of 90% with significance level of 0.05, a total of 210 and 297 measurements, respectively, are necessary. In addition, challenges in measuring infants with pQCT may occur. According to previous studies, small children suffer from an average of 6 infections annually. In order to detect a decrease from 12 to 9 infections during the 24-month study period, a sample size of 220 in each group is required. We estimate a possible drop-out rate of 20%. Taking into consideration all the aforementioned aspects, the trial is designed for 1000 subjects: 500 subjects in each intervention group.

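### The MANCOVA for bone strength leaves outcome vector, visit, missing scans and reported estimate unstated, and on either reading does not use every pQCT scan for the 2-year comparison

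*Combined protocol and SAP*

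**What the plan says.** The protocol's Primary outcomes section reads: "Primary outcomes of the study are bone strength measured by peripheral quantitative computed tomography (pQCT) and incidence of parent-reported infections at age 2 years". The closing phrase on age may govern bone strength as well as infections, but the sentence does not settle this. The Follow-up section sets two scans: "Bone strength of participants is evaluated by pQCT at 1 and 2 years of age".

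The main SAP's sample size section names the bone parameters and the target: "We aim at detecting a 0.2 SD unit difference between continuous bone strength parameters; bone mineral content and cross-sectional area". It then adds that "challenges in measuring infants with pQCT may occur", without a rate, and allows for 20% drop-out.

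The main SAP's Statistical methods section gives the bone analysis in a single sentence: "For continuous variables (bone strength), differences between intervention groups are assessed with multivariate analysis of covariance (MANCOVA"). It lists no outcome variables, visit, covariates, missing-scan rule or summary estimate. For other outcomes the same paragraph is more specific: serum 25-hydroxyvitamin D "concentration is analysed with linear mixed model", and infections are analysed over person-months so that all available follow-up counts. It promises intention-to-treat and per-protocol analyses of the main outcomes.

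**The concern.** A standard MANCOVA needs every element of the outcome vector, and every covariate, for each child it includes. The SAP does not define the vector, so two readings are open. With both visits in the vector, one failed or missed scan removes the child. With only the 2-year scan in it, a child who was scanned at 1 year but not at 2 years contributes nothing, and the 1-year value does not sharpen the 2-year comparison. Neither reading uses every scan.

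The second issue is the estimate. The trial was sized on a 0.2 SD difference in each of two named parameters. The test that defines MANCOVA is an omnibus test on the vector, and the SAP does not commit to reporting the difference in either parameter.

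At stake are some precision on a primary outcome and the freedom to choose vector, visit and missing-data handling after the data are seen.

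**Working it through.** **The plan's own figure.** The SAP states: "In order to reach a statistical power of 90% with significance level of 0.05, a total of 210 and 297 measurements, respectively, are necessary". For two parallel groups, n per arm = 2 × ((1.960 + 1.282)/0.2)² ≈ 526, about 1,052 in total. The stated figures do not follow from the stated inputs for a two-group comparison. That is a separate matter, but it means the figures cannot serve as evidence of slack here. The check below uses the number of children likely to be available.

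**Inputs.**
- From the SAP: 500 per arm, 20% drop-out, target 0.2 SD, alpha 0.05 (taken as two-sided). So 500 × 0.8 = 400 per arm.
- Assumed, not in the documents: the same 400 per arm attend both visits; 80% of scans are valid, independently at each visit; the between-visit correlation ρ is 0.5 to 0.8; missing scans are random given the other visit; no multiplicity adjustment yet.

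**Children per arm by pattern.** Both scans: 400 × 0.8² = 256. Only 2 years: 400 × 0.8 × 0.2 = 64. Only 1 year: 64. Valid at 2 years: 256 + 64 = 320. At least one scan: 384.

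**Effective n for the 2-year mean in a mixed model** (saturated arm-by-visit means, generalised least squares). Let k = 256/(1 − ρ²) and I = k + 64. Then n_eff = I − (kρ)²/I.
- ρ = 0.3: k = 281.3, I = 345.3, n_eff = 345.3 − 84.4²/345.3 = 325
- ρ = 0.5: k = 341.3, I = 405.3, n_eff = 405.3 − 170.7²/405.3 = 333
- ρ = 0.8: k = 711.1, I = 775.1, n_eff = 775.1 − 568.9²/775.1 = 358

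**Power** = Φ(0.2 × √(n/2) − 1.960), for one parameter at 2 years:

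| Analysis | n per arm | Power |
|---|---|---|
| No failed scans | 400 | 80.7% |
| MANCOVA vector spans both visits | 256 | 61.9% |
| 2-year scans alone | 320 | 71.6% |
| Mixed model, ρ = 0.3 | 325 | 72.2% |
| Mixed model, ρ = 0.5 | 333 | 73.3% |
| Mixed model, ρ = 0.8 | 358 | 76.2% |

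The standard error with 2-year scans alone exceeds the mixed model's by √(333/320) − 1 ≈ 2% to √(358/320) − 1 ≈ 6%. With a two-visit vector the excess is √(333/256) − 1 ≈ 14% to √(358/256) − 1 ≈ 18%.

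**Range over scan validity** (same formulas, ρ = 0.5 to 0.8):

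| Valid scans | Two-visit vector | 2-year alone | Mixed model |
|---|---|---|---|
| 90% | 72.1% | 76.5% | 77.5% to 78.9% |
| 80% | 61.9% | 71.6% | 73.3% to 76.2% |
| 70% | 50.8% | 65.8% | 68.2% to 72.4% |

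**Multiplicity.** Two separate tests at 0.05 give a family-wise error of 1 − 0.95² = 9.75% if independent, and less if the parameters are positively correlated. Under Holm, the smaller p-value is tested at 0.025 (critical value 2.241). At that level, power for one parameter at 80% validity is Φ(0.2 × √(333/2) − 2.241) = 63% at ρ = 0.5 and 67% at ρ = 0.8. For 2-year scans alone it falls from 72% to 61%. If one parameter is rejected, the other is tested at 0.05.

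**The case against.** MANCOVA is a recognised method for correlated bone parameters, and using a mixed model for 25-hydroxyvitamin D does not make a different choice for bone an error. The natural reading is bone mineral content and cross-sectional area at 2 years. If both come from the same scan they tend to be missing together, so little is lost beyond the failed scans. On that reading the gain is about 2 to 5 points of power, and under 1 point at ρ = 0.3. This stands, and it is why the 62% figure is conditional. The joint test also covers both parameters at one alpha, which two separate models do not. That stands too, and the fix has to answer it.

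Four stronger readings are tempting, and the documents do not support them.
- A reader might infer that MANCOVA yields no mean difference. Only the omnibus statistic lacks one; the same fit gives an adjusted group coefficient and standard error for each parameter, and the SAP also lists t-tests for group comparisons. What is missing is a commitment to report the difference.
- A reader might infer that children with a missed visit are certain to be deleted, or that the 1-year scans are thrown away. The vector is undefined, and nothing bars a separate 1-year analysis.
- A reader might infer that scan failures are expected at some known rate. The SAP says only that difficulties may occur, and cites them among the reasons for enrolling 1,000.
- A reader might infer bias. Restless children would be hard to scan in both arms. Bias in the randomised contrast needs missingness related to arm, or a different effect in the unscanned children, and the documents show neither.

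**Conclusion.** The point holds as one of under-specification together with an avoidable loss of information on a primary outcome. No reading of the MANCOVA sentence brings every scan to bear on the 2-year comparison, and the SAP does not say which reading applies or promise the estimate on which the trial was sized.

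The size depends on the reading. Under the assumptions above, a mixed model has 73% to 76% power for 0.2 SD. That compares with 72% if MANCOVA's vector is the 2-year scan, which the Primary outcomes sentence favours, and 62% if it spans both visits. The documents give no scan-failure rate and no between-visit correlation, so these figures illustrate the range and are not forecasts. The case for changing the plan rests as much on fixing vector, visit, missing-data handling and estimate in advance as on the power gain.

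**What to change.** Replace the bone sentence in the main SAP's Statistical methods with text to this effect:

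*Bone mineral content and cross-sectional area are each analysed with a linear mixed model for repeated measures (1 and 2 years) with arm, visit, arm × visit and sex (the randomisation stratum) and an unstructured covariance, including every child with at least one valid scan. The primary estimate for each is the adjusted mean difference at 2 years with 95% CI, also in SD units. The two primary bone tests are controlled by Holm's procedure.*

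An alternative to Holm is to keep the MANCOVA omnibus test as gatekeeper, with its vector and visit defined, and to test each parameter only if it is significant. Any covariates beyond sex should be named in advance.

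**Cost.** SAP wording and modest programming; no new data. The model assumes scans are missing at random given the other visit, and it recovers nothing for a child with no scan. Multiplicity control has a price per parameter: at Holm's first step it is about 9 to 10 points under the assumptions above, more than the precision gain over 2-year scans alone. That price comes from making two separate claims and applies equally to per-parameter tests on 2-year scans alone. The cost of a gatekeeper depends on the correlation between the two parameters, which the documents do not give.

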### Participants and methods

A total of 1 000 families are recruited and informed consent is obtained 1-2 days after the delivery at the Kättilöopisto Maternity Hospital in Helsinki. We include white northern European women with a singleton pregnancy and without regular medication. Healthy infants born at term (37-42 weeks) and with weight appropriate for gestational age are included in the study. Exclusion criteria for the infants are: seizures, need for early antibiotic

treatment, need for nasal continuous positive airway pressure > 24 hours, extended phototherapy > 72 hours, need for nasogastric tube > 24 hours or intravenous glucose infusion. Data on family background (parents' socio-economic status, health, lifestyle factors) and maternal dietary status are documented with a questionnaire. At birth, a cord blood sample (20 ml) is taken and stored for later analyses.

Participating infants are randomised to receive either the currently recommended vitamin D3 supplementation of 10 µg (400 IU) daily or a higher dose of 30 µg (1200 IU) daily from age 2 weeks to 2 years. Boys and girls are randomised separately in blocks of 50. Randomisation is performed by the Helsinki University Hospital Pharmacy. The study is double-blinded. Vitamin D is administered orally as vitamin D3, with a dose of 5 drops a day for both concentrations.

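### Neither primary model names a baseline covariate, not even the randomisation stratifier sex; a short pre-dose list would add modest precision and keep post-randomisation variables out

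*Combined protocol and SAP*

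**What the plan says.** The original SAP, under Statistical methods, gives one sentence to each primary analysis.

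- **Infections:** "For evaluating the effect of vitamin D supplementation on the frequency of infections, negative binomial model is applied". The next sentence brings in follow-up as person-months. No covariate is named.
- **Bone:** "differences between intervention groups are assessed with multivariate analysis of covariance (MANCOVA". This is a covariate method, but no covariates are listed.

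In that section, covariates are mentioned only for the 25-hydroxyvitamin D mixed model. The later amendments mention them for the neurodevelopmental and psychiatric outcomes, which does not reach infections or bone.

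The Protocol, under Participants and methods, shows what is known before dosing starts at 2 weeks:

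- "Data on family background (parents' socio-economic status, health, lifestyle factors) and maternal dietary status are documented with a questionnaire".
- "Healthy infants born at term (37-42 weeks) and with weight appropriate for gestational age are included in the study". Applying this criterion requires gestational age and birth weight for every child.
- Date of birth must be known, since consent follows delivery by 1–2 days and dosing is timed by age.
- Boys and girls are randomised separately, in blocks of 50.

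For the infection outcome, the SAP's sample size section states that "a sample size of 220 in each group is required" to detect a fall from 12 to 9 infections over 24 months.

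**The concern.** Three things are at stake.

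1. **Precision.** The infection sample size only makes sense if counts vary far more than Poisson. Longer follow-up does not remove variation that comes from stable differences between children, but baseline predictors can remove some of it. Bone mineral content and cross-sectional area depend on body size, so birth size is a natural pre-randomisation predictor.
2. **The stratifier.** If sex predicts the outcome and is left out of the model, the precision gained by stratifying on it is not carried into the standard error.
3. **An open list.** A MANCOVA without named covariates leaves the choice until after the data are seen and sets no rule against post-randomisation variables. The bone sample size cites a study on time since onset of walking and tibial strength, so walking age or current body size could look like obvious covariates. Both are measured after dosing starts, and the Protocol Background links vitamin D status to growth and motor development. Adjusting for them could remove part of a real effect.

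**Working it through.** **Inputs from the SAP sample size section.** 12 versus 9 infections; 220 per group; 500 per group with 20% drop-out, so 500 × 0.8 = 400; bone target 0.2 SD.

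**Assumptions.** The 90% power and 0.05 level are stated only in the bone sentence ("In order to reach a statistical power of 90% with significance level of 0.05, a total of 210 and 297 measurements, respectively, are necessary"). I carry them over to infections and take the test as two-sided. The shares explained by covariates (R for infections, R² for bone) are also mine; the documents give neither.

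**Infections: inverting the plan's figure.** The 220 cannot be reproduced forwards, because no SD or dispersion is given. I therefore solve for the dispersion k:

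n = (z₁ + z₂)² × (1/12 + 1/9 + 2k) / [ln(9/12)]²

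- (1.960 + 1.282)² = 10.507; [ln 0.75]² = 0.0828; 1/12 + 1/9 = 0.194.
- The bracket must equal 220 × 0.0828 / 10.507 = 1.733.
- k = (1.733 − 0.194)/2 = 0.769.
- Extra-Poisson share = 1.538/1.733 = 88.8%.

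| Assumed power | k | Extra-Poisson share |
|---|---|---|
| 80% | 1.063 | 91.6% |
| 90% | 0.769 | 88.8% |
| 95% | 0.603 | 86.1% |

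Pure Poisson counts would need only about 25 per group at 90% power, so heavy overdispersion is implied under any of these choices.

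**Infections: effect of covariates.** Replace k by k(1 − R), with k = 0.769:

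| R | Bracket | Variance vs unadjusted | Equivalent n per group | SE vs unadjusted |
|---|---|---|---|---|
| 0 | 1.733 | 1 | 220 | 1 |
| 10% | 1.579 | 0.911 | 201 | 0.955 |
| 20% | 1.425 | 0.822 | 181 | 0.907 |

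Here R is the share of k removed. If 10% and 20% are instead shares of a lognormal between-child variance on the log scale, ln(1.769) = 0.570, the remaining k is exp(0.513) − 1 = 0.671 or exp(0.456) − 1 = 0.578. The variance then falls by 11% or 22%.

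**Infections: practical size at 400 per group.** Power = Φ(|ln RR|/√(bracket/400) − 1.96).

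- At the planned ratio of 0.75, unadjusted power is 99.2% (k = 0.769) or 96.5% (k = 1.063).
- A 95% interval centred on 0.75 is 0.659–0.853 unadjusted, 0.663–0.848 with R = 10% and 0.667–0.843 with R = 20%.
- At a ratio of 0.85 (my choice; means 12 and 10.2), power is 70% unadjusted, 74% with R = 10% and 78% with R = 20%. With k = 1.063 it is 57%, 61% and 66%.

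**Bone.** For 0.2 SD at 90% power, an unadjusted two-group comparison needs 2 × 10.507/0.04 = 525.4, so 526 per group. The SAP's totals of 210 and 297 are not reproduced this way, so I use the formula and not those totals. Power = Φ(0.2 × √(n/2)/√(1 − R²) − 1.96):

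| n per group | R² = 0 | 5% | 9% | 16% |
|---|---|---|---|---|
| 400 | 80.7% | 82.7% | 84.3% | 87.0% |
| 320 | 71.6% | 73.7% | 75.6% | 78.8% |

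The 320 row assumes that a further 20% of completers have no usable scan. The SAP expects measurement difficulties but gives no rate.

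**The case against.** An unadjusted comparison in a randomised trial of this size is valid, so adjusting for efficiency is partly a matter of preference. That stands: no bias is alleged here. Several stronger readings are tempting, and the documents do not support them.

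- **That the plan excludes covariates from the infection model.** It is silent on them; it does not specify a model of arm alone.
- **That 89% of the infection variance is planned between-child variation.** The SAP gives no dispersion. The figure is back-calculated under a borrowed power, and it is extra-Poisson variance, to which clustering of episodes within a child also contributes. It does not show how much the recruitment data would explain. Restriction to term infants of appropriate weight narrows birth size, and about two full years of follow-up weakens season of birth, so modest values are plausible.
- **That the infection comparison is short of power.** At the planned effect it is not, with 400 per group.
- **That the bone analysis gives precision away.** MANCOVA presupposes covariates. The 81% describes an unadjusted comparison that the SAP does not specify for bone, so the gain over the real plan could be nil.
- **That the sponsor intends to adjust for walking age or current size.** Neither is proposed; walking appears only in a reference title. The Background's motor-development link concerns severe deficiency, not the two doses compared here. The risk comes from an open list, not from a stated intention.

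It is also fair that birth weight and gestational age appear only as eligibility conditions. That they are on file is an inference, though a safe one.

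**Conclusion.** The point holds as a gap in prespecification with a modest, nearly free gain in precision. Neither primary model names a baseline covariate, and neither names sex.

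For infections, an assumed 10–20% of dispersion explained would cut the variance of the log rate ratio by about 9–18%. This matters for interval width and for effects smaller than the planned 25% reduction, not for power at the planned effect.

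For bone, unadjusted power at 400 per group is about 81%. Covariates explaining an assumed 5–16% would bring it to 83–87%, but the improvement over the planned MANCOVA cannot be stated until its covariates are listed. The firmer reason to act on bone is to fix the list and confine it to pre-dose variables.

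The infection figures rest on carrying over the 90% power and two-sided 0.05; the extra-Poisson share stays at 86–92% for power from 95% to 80%. The shares explained by covariates are assumptions throughout.

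**What to change.** Add to the original SAP, under Statistical methods, wording such as:

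> Both primary models include sex (the randomisation stratifier). The infection model also includes season of birth and a short list of named recruitment-questionnaire items, fixed before unblinding. The bone model also includes birth weight and gestational age. Only variables measured before the first dose enter these models. Missing baseline items are handled by single imputation or a missing indicator. The unadjusted estimate is reported as a sensitivity analysis.

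The questionnaire items should be named one by one, since naming whole domains would leave the choice open. Season is preferable to month of birth, which could add 11 parameters.

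The cost is one SAP paragraph, a few extra parameters and one extra model run per outcome. No new data collection should be needed, provided birth weight and gestational age were kept from the eligibility check.

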**PROTOCOL**

**Background**

Lower vitamin D concentrations are associated with neurodevelopmental disorders, including autism spectrum disorder (ASD) and attention-deficient hyperactivity disorder (ADHD) in children. Associations between vitamin D concentrations and cognitive and motor functioning has not been systematically found. However, previous evidence is based on observational studies and no causal relationship can be inferred. Randomized controlled trials (RCT), as well as non-randomized trials, on vitamin D supplementation in children have been small-scale studies, focused typically on symptom severity among children with ASD or ADHD, and reported mixed findings. Further studies are needed to test whether vitamin D supplementation from infancy on in healthy community-based children provides benefits on neurodevelopment.

**Primary outcomes**

Primary outcomes of the study are developmental milestones measured with the Ages and Stages Questionnaire (ASQ) at age 12 and 24 months and social-emotional problems and competencies measured with Infant-Toddler Social Emotional Assessment (ITSEA) at age 24 months.

**Follow-up**

Participants are assessed at a study outpatient clinic by a study nurse and/or pediatrician at 12 months and 24 months of age. Data on developmental milestones are collected with Ages and Stages Questionnaire (ASQ) at 12- and 24-month and data on social-emotional problems and competencies with Infant-Toddler Social Emotional Assessment (ITSEA) at 24-month follow-ups. Blood samples are taken for biochemistry. Families are provided study diaries where they keep daily records on dosing of vitamin D3 supplement.

